### Intervention description

The intervention has two parts: a clinical intervention and a practice-level intervention.

Clinical intervention: This will be delivered over a 6-month period by GPs and PNs acting as prevention navigators. As recommended by *the Guidelines,* other guidelines and other research, the clinical intervention is based on the 5As framework [2,4,5,7], comprising: (i) Assessment of health literacy, obesity, dietary habits, physical activity levels and readiness to change (ii) Advice on risk of being overweight and lifestyle changes (iii) Agreement on realistic weight loss, diet and physical activity goals (iv) Assisting by referral to services and/or programs and (v) Arranging follow-up telephone calls and visits to review progress. Steps i-iv will be delivered at a health check visit about 2 weeks after the health literacy screening and enrollment of patients in the trial (Figure 1).

**Figure 1 Fig1:**
[figure not shown]
**Patient involvement.**

Practice-level intervention: This is focused on engaging the practice in implementing the clinical approach stated above with obese patients with low health literacy. In this regard two interactive face-to-face meetings will be held at individual practices. At the first meeting, reports which are based on a baseline clinical record audit will be discussed. The Chief Investigators will use the clinical audit data as a prompt to discuss strategies for improvements in primary cardiovascular disease (CVD) risk factor assessment and management specifically for obese patients based on *the Guidelines*. At another meeting, results from the health literacy screening will be discussed to raise the awareness of the health professionals of the prevalence of low health literacy amongst their patients and the need to pay special attention to these patients.

There will be a 3-hour interactive group training of GPs and PNs in providing weight management to obese patients with low health literacy. This session will include case scenario discussion and role plays. At this training, the intervention group will be provided with a copy of *the Guidelines*.

The other major component of the practice-level intervention is to develop the role of the PNs as prevention navigators. The principal role of a prevention navigator is to work with patients to set goals, provide information and support to choose appropriate referral options (including group programs and telephone coaching), overcome barriers to attendance at this referral and arrange follow up. This is a new potential role for PNs in Australian general practice although there have been some previous examples of the use of community navigators in screening and prevention [29-31].

We will train PNs in their role as prevention navigators and in the conduct of the health check visit. Training will focus on communication with patients with low health literacy and facilitating goal setting, referral navigation and arranging follow up visits.

Educational meetings will also be held for GPs in the control group. However, the educational messages delivered will not be in the same context of obesity management as for the intervention group. For example, at the clinical audit result discussion, emphasis will be on CVD risk factor recording and management. The control group will also be provided with a copy of *the Guidelines*.

### Ethics

Ethics approval has been granted by the UNSW Australia Human Research Ethics Advisory Panel and the University of Adelaide Human Research Ethics Committee. All participants will give written informed consent.

### Data collection

#### Evaluation of general practitioners and practice nurses

Data will be collected at baseline and 12 months to compare intervention and control groups through surveys and interviews and will afford linkage with patient-level data. PNs will be additionally interviewed about prevention navigation at 12 months only.GP and PN Surveys: A validated self-completed questionnaire [32] which was modified for our previous research [12] has been further adapted for this trial. The questions relate to the assessment and management of CVD risk factors and GP and PN confidence in managing obese patients with low health literacy. We have included questions to assess GP and PN attitudes, beliefs and practices regarding obesity management [33] and their knowledge about obesity assessment.GP and PN Qualitative Interviews: GPs and PNs will be invited to participate in qualitative interviews. The interviews will assess their provision of preventive care to obese patients with low health literacy including the perceived facilitators and barriers and educational needs for effective management of obesity. In addition, we will explore how patient ethnicity affects their weight management.

Additional questions will explore the role of PNs in helping patients navigate community-based lifestyle referral services for weight loss and the perceived facilitators and challenges in doing so. Barriers that patients face in accessing referral services will also be discussed.

#### Evaluation of patients

All patients will be surveyed at baseline, 6 and 12 months. In the intervention group, a subsample of Arabic and English-speaking patients will also be interviewed at baseline and 12 months. Data on anthropometric measures will be collected at baseline and 12 months.Patient Surveys: A questionnaire will be administered by telephone in English or in the language in which patients completed the health literacy screening questionnaire. The survey used at baseline and 12 months includes the following five sections:i.Assessment of lifestyle-related risk factors and management by primary healthcare providers and patient’s stage of change.ii.The 12-item short form – the SF-12® Health Survey – with a 4-week recall to measure eight health-related quality of life domains: physical functioning; role-physical; bodily pain; general health; vitality; social functioning; role-emotional; and mental health [34].iii.Health Literacy Questionnaire to assess patients’ general health literacy needs and challenges. This questionnaire covers nine conceptually distinct areas of health literacy that capture a wide range of the lived experiences of people attempting to engage in understanding, accessing and using health information and health services [35]. The domains are: feeling understood and supported by healthcare providers; having sufficient information to manage my health; actively managing my health; social support for health; appraisal of health information; ability to actively engage with healthcare providers; navigating the healthcare system; ability to find good quality health information; and understanding health information well enough to know what to do.iv.Impact of Weight on Quality of Life-Lite (IWQOL-Lite) [36], a validated, 31-item, self-report tool, to measure obesity-specific quality of life. In addition to a total score, there are scores on five domains: physical function; self-esteem; sexual life; public distress; and work.v.Demographic questions such as age, sex, and country of birth.At 6 months, patients will be administered a shortened version of the survey covering only assessment and management of lifestyle-related risk factors and stage of change.Patient Interviews: A subsample of Arabic and English-speaking patients, in the intervention group, will be qualitatively interviewed over telephone. The aim for this interview is to explore ethnicity-related factors which influence health literacy for weight management.Anthropometric Measures: At baseline, at the time of patient enrollment, GPs will check patient weight and height and calculate BMI. This information will be recorded on the enrollment form. At 12 months, the research team will send invitation letters to patients to attend their practice for final data collection. After two weeks, reminders will be sent to patients who have not responded to the initial invitation. At this visit, data will be collected on weight, BMI and current use of medicines which could impact body weight.

Besides the data collected through surveys, interviews and anthropometry, we will also collect data from clinical records, health literacy screening and health checks.Clinical Record AuditsAudits of clinical records will be conducted at the baseline and 12 months in all practices. Electronic records of patients, aged 40–70 years, under the care of participating GPs will be audited for CVD risk factors with a tool that allows unidentifiable data extraction [37]. The CVD risk factors include: weight, height, BMI, waist circumference, smoking status, alcohol consumption, blood pressure, lipids and 5-year absolute CV event risk. All GPs will be sent reports based on the clinical record audit results. The reports for the intervention and control groups will, however, cover different aspects of the clinical audit results.Health Literacy ScreeningHealth literacy screening will take place in all the participating practices. Patients, 40–70 years old, will be screened over a 4-week period using a questionnaire, as described earlier. The self-administered questionnaire is scored on a 5-point 1–5 scale [27]. Scores for the three screening questions will be dichotomised into adequate (3–10) or low health literacy (>10) [27]. Patients whose score of the question *‘How confident are you filling in medical forms by yourself?’* is ≥3, will also be categorised as having low health literacy [25].The screening will identify patients who have low health literacy and who will be potentially eligible for recruitment.Health ChecksHealth checks will take place in intervention practices only. At the health check visit, prevention navigators will collect data on risk assessment which will include weight, BMI, waist circumference, dietary habits and physical activity. Patients will be assessed for readiness to change their weight and barriers to changing diet and physical activity will be determined. Weight, diet and physical activity goals will be set and recorded. The assessment data will help the prevention navigators to tailor their advice to the patients’ need and to help patients decide about their referral to community-based lifestyle modification programs/services. Data on goal setting will be used to determine patient’s progress against the goals at follow-up visits.

### Outcomes

The proposed primary outcome measures are:PNs’ self-reported behaviour and confidence in assessing obese patients with low health literacy and providing advice and referral to community-based lifestyle modification programs for weight loss.Patients’ report, in past six months, of receiving assessment, advice and referral for weight loss and attending/using community-based weight loss lifestyle modification programs referred to.Patient health literacy related to weight loss.

The proposed secondary outcome measures are:Patient self-reported (i) intake of dietary portions of fruit and vegetables per day, (ii) use of high fat food per day, (iii) hours of sedentary activity per day, (iv) consumption of alcohol, and (v) minutes of moderate and/or vigorous intensity physical activity per week.Measured weight.Health-related quality of life.The total cost of health service use.

### Sample size and data analysis

Estimates for sample size based on intra-cluster correlation coefficients for clustering, prevalence, variance and effect sizes from our previous research are in Table 2. Sample size estimates are based on a two-sided test of significance at α = 0.05. β = 0.8 and 20% loss to follow up and effect sizes and standard deviations based on our previous research [38,39].

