**Table 2 Tab2:** **Estimates of sample size for primary and secondary outcomes**

**Outcome**	**Intra-cluster correlation coefficient**	**Design effect (30 patients per practice)**	**Effect size/different proportions**	**Sample size estimate for each group**
Advice on diet	0.051	2.48	25%	170
Advice on physical activity	0.035	2.02	25%	140
Referral/attendance diet	0.026	1.75	25%	115
Referral/attendance physical activity	0.011	1.32	25%	80
Mean health literacy score	0.014	1.41	0.4	140
Mean diet score	0.001	1.03	0.4	115
Mean physical activity score	0.018	1.52	0.4	150
Mean BMI	0.038	2.10	0.5	135

We will examine change in the outcomes between intervention and control practices, after adjusting for baseline differences. We will analyse patient variables for within and between practice differences using multilevel linear and logistic regression techniques that adjust for clustering by practice and multiple imputation to adjust for missing values. Analyses will be on an intention to treat basis.

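### Three of the four continuous-outcome rows of Table 2 match a calculation without the stated 20% loss, the diet row matches no version, and power is misprinted as β

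*Protocol article*

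**What the plan says.** Under *Sample size and data analysis*, the Protocol article gives the basis of all the estimates: "Sample size estimates are based on a two-sided test of significance at α = 0.05", followed by "β = 0.8 and 20% loss to follow up and effect sizes and standard deviations based on our previous research". Table 2 then lists, for each outcome, an intra-cluster correlation (ICC), a design effect for 30 patients per practice, an effect size and a final column headed "Sample size estimate for each group". Two of the four continuous rows read "Mean health literacy score 0.014 1.41 0.4 140" and "Mean diet score 0.001 1.03 0.4 115". The other two are physical activity (ICC 0.018, design effect 1.52, effect size 0.4, 150 per group) and BMI (0.038, 2.10, 0.5, 135 per group). Nothing marks the final column as a number analysed after loss. Health literacy is listed among the primary outcomes.

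The recruitment target is stated separately. The Abstract and the *General practices* section plan 20 practices, and the Abstract plans 20 to 40 patients in each.

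**The concern.** The text names 20% loss as one of the inputs, so each tabulated size should be about a quarter larger than the size needed for analysis. If the loss was left out, the tabulated numbers are too small as enrolment figures for the power intended. One of the affected rows is the only continuous primary outcome in the table. Separately, β is the type II error rate, so β = 0.8 read literally means 20% power. A reader who relies on Table 2 to judge the design, or to reuse its figures, would be misled about what those sizes deliver.

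**Working it through.** **Inputs.** Two-sided α = 0.05 and 20% loss come from the sample size text. ICCs, design effects (DE) and effect sizes (d) come from Table 2. Two readings are assumed: d is in standard deviation units, and β = 0.8 means power 0.80. The literal reading, 20% power, would give only 17 to 25 per group before loss, far from any row.

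**Design effects.** 1 + 29 × ICC gives 1.406, 1.029, 1.522 and 2.102 for health literacy, diet, physical activity and BMI. These round to the tabulated 1.41, 1.03, 1.52 and 2.10.

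**Size before clustering.** n = 2(1.960 + 0.842)²/d² = 98.1 per group for d = 0.4 and 62.8 for d = 0.5.

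**Size with clustering, without and with loss (per group):**

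| Row | Stated | n × DE, no loss | ÷ 0.8 | × 1.2 |
|---|---|---|---|---|
| Health literacy | 140 | 98.1 × 1.406 = 137.9 | 172.4 | 165.5 |
| Diet | 115 | 98.1 × 1.029 = 101.0 | 126.2 | 121.1 |
| Physical activity | 150 | 98.1 × 1.522 = 149.3 | 186.7 | 179.2 |
| BMI | 135 | 62.8 × 2.102 = 132.0 | 165.0 | 158.4 |

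Rounded up to the next 5, the no-loss results for health literacy, physical activity and BMI are exactly the stated 140, 150 and 135. With loss, by either convention, no row is reproduced. Diet is not reproduced in any column.

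**Power if the tabulated numbers are enrolled and 20% are lost.** Power = Φ(d√(m/2) − 1.96), with m = 0.8 × stated n/DE:

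- Health literacy: m = 112/1.406 = 79.7, power 71%.
- Diet: m = 92/1.029 = 89.4, power 76%.
- Physical activity: m = 120/1.522 = 78.8, power 71%.
- BMI: m = 108/2.102 = 51.4, power 72%.

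If 30 are enrolled and 24 analysed per practice, the design effects fall to 1 + 23 × ICC = 1.322, 1.023, 1.414 and 1.874. Power is then 74%, 76%, 74% and 77%. If the tabulated numbers are instead all analysed, power is about 80%, 85%, 80% and 81%.

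**Sizes that include the loss.** With the tabulated design effects, rounded up: 173, 127, 187 and 165 per group (health literacy, diet, physical activity, BMI). With the design effect at 24 analysed: 98.1 × 1.322/0.8 = 162.1, and likewise 125.5, 173.4 and 147.1, so 163, 126, 174 and 148.

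**Against planned enrolment.** With 1:1 allocation (assumed; the ratio is not stated), 10 practices × 20 to 40 patients = 200 to 400 per group. At the lower end 0.8 × 200 = 160 remain, and power with the tabulated design effects is 85%, 94%, 83% and 87%. At 30 per practice, 240 remain and power is 96%, 99%, 94% and 97%.

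**The case against.** The strongest reply is that nothing in the trial depends on the error. Enrolment is set by practices and patients per practice, it exceeds every corrected size, and the article reports that baseline data collection is complete. Power of 71% to 76% would arise only if exactly the tabulated numbers were enrolled, which is not the plan. This stands, and it settles the severity.

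The tabulated figures may also have been meant as analysed numbers. That would make three rows right, but the text would then be wrong to list loss as an input, and diet would still not fit.

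The dropped input need not be the loss. A one-sided 5% test with 20% loss gives 135.8, 147.0 and 130.0 for the same three rows, nearly as close. Since the text says two-sided, one stated input was not applied either way; which one is for the sponsor to confirm.

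The analysis adjusts for baseline, which could recover power. If residual variance falls by the factor 1 − ρ², 80% power after loss needs ρ² of at least 1 − 0.8 × stated n/no-loss n. That means ρ from about 0.30 (diet, 1 − 92/101.0) to 0.44 (physical activity, 1 − 120/149.3). Such correlations are possible, but the article states none and does not use one in the sizing.

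Some stronger readings are tempting but unsupported:

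- A reader might infer that all four continuous rows omit the loss. Diet lies about 14% above its no-loss size (115/101.0), so for that row only a failure to reproduce is shown.
- A reader might infer that the β wording causes the shortfall. The sizes were plainly computed at 80% power, so it is a slip of notation.
- A reader might infer that the table mixes rows with and without loss, because the two advice rows (170 and 140) fit a calculation with loss at 25% v 50% (170.2 and 138.4). Those rates are assumed, and a no-loss calculation with continuity correction at 37.5% v 62.5% fits as well (172.0 and 140.1).
- A reader might infer that the largest requirement is misidentified. The article names no governing row.

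**Conclusion.** The text and Table 2 disagree. Under the stated two-sided 0.05 test at 80% power, the health literacy, physical activity and BMI rows carry no loss allowance, and the diet row cannot be reproduced. As enrolment figures the four rows would give about 71% to 76% power, or 74% to 77% with 24 analysed per practice. This rests on standardised effect sizes, β = 0.8 meaning power 0.80, and an unadjusted comparison.

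A reader might conclude that the trial is underpowered. The article does not support that: with 1:1 allocation, even 20 patients per practice leaves power at about 83% or more for all four outcomes after 20% loss. This is a minor correction of stated figures, though one of them belongs to a primary outcome.

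**What to change.** 1. Replace the β statement with power = 0.80 (β = 0.20).
2. Have the sponsor confirm from the original calculation which stated input, the two-sided test or the 20% loss, was not applied, and how the diet figure arose.
3. Then choose one of two equally valid repairs. Either restate the continuous rows as enrolment numbers with 20% loss: 173 (health literacy), 127 (diet), 187 (physical activity) and 165 (BMI) if 30 per practice are analysed, or 163, 126, 174 and 148 if 30 are enrolled and 24 analysed. Or label the column as numbers analysed after loss, take 20% loss out of the list of inputs to it, and recompute diet (101.0 before rounding).
4. State the resulting requirement beside the planned 200 to 400 per group, with the allocation ratio.

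The cost is an edit to one sentence and one table. No extra patients or practices are needed. The only loss is that the margin between requirement and plan looks somewhat smaller.

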**Table 2 Tab2:** **Estimates of sample size for primary and secondary outcomes**

**Outcome**	**Intra-cluster correlation coefficient**	**Design effect (30 patients per practice)**	**Effect size/different proportions**	**Sample size estimate for each group**
Advice on diet	0.051	2.48	25%	170
Advice on physical activity	0.035	2.02	25%	140
Referral/attendance diet	0.026	1.75	25%	115
Referral/attendance physical activity	0.011	1.32	25%	80
Mean health literacy score	0.014	1.41	0.4	140
Mean diet score	0.001	1.03	0.4	115
Mean physical activity score	0.018	1.52	0.4	150
Mean BMI	0.038	2.10	0.5	135

We will examine change in the outcomes between intervention and control practices, after adjusting for baseline differences. We will analyse patient variables for within and between practice differences using multilevel linear and logistic regression techniques that adjust for clustering by practice and multiple imputation to adjust for missing values. Analyses will be on an intention to treat basis.

### Project management

The trial will be led by a project management committee which comprises the investigators, the project coordinator and field researchers and meets bimonthly. In each city a working group manages the field operations in collaboration with their own Medicare Local.

### Trial status

The trial is registered with the Australian Clinical Trials Registry ACTRN12614001021662.

The trial is underway with baseline data collection completed and the intervention commenced.

## Discussion

The BMWGP trial aims to evaluate the implementation and effectiveness of PNs acting as prevention navigators supporting obese patients with low health literacy to better manage their weight. This has the potential to address both the infrequency of referral for obese patients in Australian primary care and the barriers to preventive care experienced by patients with low health literacy through an intervention at both the clinical and practice levels. It also has significant implications for the role of PNs and other health professionals in preventive care in general practice and will inform current discussion of how this role needs to develop in the future [40,41].
